### 7.3. Study Investigational Product

#### 7.3.1. Device Overview

The Twin Stim® Plus Digital TENS/EMS (HC [License name](#): TWIN STIM SERIES) can be used both with the battery and plugged in. In this study, the plug in will be used because the device does not need to be portable, the battery charge will not be a variable/concern, and to access the battery compartment would need to disassemble a component of the stimulation system. The unit sends electrical impulses via electrodes to the body and reach the nerves and underlying muscle group. This unit is a combination stimulator of TENS and EMS which can be used for muscle stimulation and pain relief. The device is provided with four controllable output channels, each independent of each other. An electrode pair can be connected to each output channel. The intensity controls are protected by a cap to avoid accidental touch. The settings are controlled by pressing buttons.

#### 7.3.2. Operation of the device

The device is provided with four controllable output channels, each independent of each other. An electrode pair can be connected to each output channel. The intensity level is controlled by press buttons. The following instruction can be followed to start the stimulation:

- 1) Plugging the device cable into any working 110 or 220/240v mains electrical outlet.
- 2) Insert the lead wires into the lead wire sockets on top of the device.
- 3) Placing the mask on the face.
- 4) Pressing the “ON/OFF button” to turn on the device.
- 5) Selecting the mode and settings as instructed.
- 6) There are 4 sets of intensity buttons, which correlate to each of the 4 channels. The individual can slowly increase or decrease the intensity by pressing the up or down Intensity buttons. Press the up-arrow button to increase the intensity and press the down arrow button to decrease intensity.
- 7) Turning the device off by pressing the “ON/OFF button” after treatment.

#### 7.3.3. Device Safety Features

For safety reasons, the Twin Stim® Plus Digital TENS/EMS device should be checked for any external damage, defective operating elements, and the usability of accessories (including cables).

## **8. Outcome Measures**

### **8.1. Primary Outcome Measures**

The primary outcome will be the feasibility, tolerability, and safety outcomes that include the recruitment, dropout, data completion, and protocol compliance rates, as well as the number and nature of AEs and SAEs. Self-report questionnaires will be completed via REDCap.

### **8.2. Secondary Outcome Measures**

Secondary outcomes will include the A) change in depression symptoms, measured by the HAM-D-17 scale and the Quick Inventory of Depressive Symptomatology (QIDS-SR-16); B) change in anxiety, measured by the Generalized Anxiety Disorder-7 (GAD-7); C) change in quality of life, measured by the World Health Organization Quality of Life Questionnaire (WHO-5); D) change in subjective sleep, measured by the Pittsburgh Sleep Quality Index (PSQI); E) HAM-D-17 response and remission rates and sustainability of effects for up to 4 weeks (28 days) following the intervention. The choice of scales in this study has been informed by our pilot study; we have added the FES experience scale. The MADRS will be used for recruitment and the HAM-D-17 will be used for the evaluation of treatment response as per current best practice in clinical trials. Self-report questionnaires will be completed via REDCap.

## **9. Potential Risks and Benefits**

### **9.1. Potential Benefits**

#### Benefit to individual participants

MDD is a common, severe psychiatric illness. However, participants in this study may experience some degree of relief from mood symptoms as a result of the FES intervention. There are no serious risks to the participant from the treatment used in this study. The chance to understand and develop a new treatment for a wide range of psychiatric disorders is an important step in helping the millions of people in the world who suffer from mental illness.

### **9.2. Potential Risks and Analysis of Risk/Benefit Ratio**

#### 3D mask

The materials used for printing the FES mask are chosen to be biocompatible and chemically stable, similar to the conventional polymeric materials used in wearables. Therefore, it is expected

that there will be no skin sensitivity to the mask's material itself. However, we will monitor the user's face after experiencing multiple courses of stimulation. If any skin reaction (e.g., redness and bruising) is observed on the user's face, we will switch to other available biocompatible materials for the mask.

Due to the potential geometrical mismatches between the mask and face, which might originate from either the scanning process or CAD design steps, there is a possibility of the user's discomfort or ineffective contact with the skin when wearing the mask. To address this issue, we will check with the user for any discomfort or geometrical mismatch when they put on the mask and determine the problematic regions. Then, we can adjust the CAD design and modify the geometry of those regions so that we can reprint and deliver a modified mask with the best design based on the functionality and user's experience.

We are using mechanically flexible and durable materials for printing the masks, which we expect to be robust and not damaged easily, e.g., if it accidentally falls down from the face. However, in case of a fracture or any other damages that may occur when using the mask, we would ask the user to stop wearing the mask and inform us about the damage type and shape. For small damages, we might be able to repair the mask by standard adhesion methods, while for large damages, we can simply print a new mask and deliver it to the user, as we already have the final 3D model design, and we can simply run the 3D printing step for a new mask mold and then create a new mask.

### Functional Electrical Stimulation (FES)

In our initial studies of FES in both healthy and MDD participants, we saw (i) no safety concerns and (ii) no AEs. Historically, transcutaneous FES has been extensively used in neurorehabilitation and AEs reported are rare and mild, such as redness/irritation of the skin underneath the stimulation site, muscle soreness, and muscle discomfort. We now propose to apply FES 5 times a week – 2 times more/week than in the pilot study for MDD, but we do not foresee any major risks/safety concerns as alluded to above. We will maintain an AE self-report and Adverse Event Log (AEL) as part of the study, to be systematically completed by the study coordinator.

### Clinical Assessments

Self-report assessments contain questions regarding sensitive personal information. This risk is necessary in order to assess mood symptoms and associated psychopathology. Subjects will be assured upon intake that only study personnel will see any rating form responses.

### Reproductive Risks

For female participants who are able to conceive, FES stimulation during pregnancy has no known risks on the ova or fetuses. However, there is always a possibility that if participants are pregnant, FES stimulation may have risks that we do not know about. For this reason, such participants should not participate in the study if they may be pregnant.

Appropriate family planning methods will be discussed with participants and decided upon in consultation with the study doctor. To confirm that a female of childbearing potential is not pregnant before starting the study, the RC will ask females if they are pregnant or planning to become pregnant throughout the duration of the study. If they become pregnant during their involvement in the study, they should immediately notify the investigators.

## **10. Data and Safety Monitoring**

### **10.1. Quality Assurance**

Methods for quality assurance will be strictly observed. A start-up meeting involving all study site RCs, co-investigators, and partners will be held prior to the study launch. Further training will be held at the site prior to commencing the study. During training, great care will be taken to fully explain the study procedures and case report form (CRF) completion.

### **10.2. Safety Oversight**

Methods for quality assurance will be strictly observed. A start-up meeting involving all study site RCs, co-investigators, and partners will be held prior to the study launch. Further training will be held at the site prior to commencing the study. During training, great care will be taken to fully explain the study procedures and CRF completion.

### **10.3. Early Withdrawal**

Participants are free to withdraw their consent and stop research study participation at any time without penalty or loss of benefits to which they are otherwise entitled. A participant's doctor may withdraw them from the study if he/she feels that it is in their best interest. The Principal Investigator may also decide to terminate the study at any time if the stimulation device is believed to be unsafe.

A study participant will be discontinued from further participation if:

- The participant fails to adhere to the study procedure.
- The participant decides not to be in this study.
- The participant misses more than two treatment visits.
- They experience worsening in depression, defined as an increase in QIDS-SR-16 score from baseline of more than 25% during two consecutive assessments, or development of active suicidal intent or attempted suicide.
- The participant meets any exclusion criteria (either newly developed or not previously recognized).

- Anything, in the opinion of the investigator, would place the participant at increased risk or preclude the participant's full compliance with or completion of the study.

If a participant withdraws or is withdrawn from the study, they will be asked questions about their experience with the FES stimulation. They will also be asked to cooperate with whatever laboratory tests or medical examinations the doctor considers necessary.

We will collect safety data on any participant discontinued because of an AE or SAE. In any case, every effort will be made to undertake protocol-specific follow-up procedures. If an AE has been reported, researchers will help the participant seek the medical care they need, and a follow-up will be performed by the Principal Investigator. In the case of an early withdrawal, the researcher will make a note to file indicating this.

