### **5.4. Retention Strategy, Costs, and Reimbursements**

Our retention strategy includes payments schedules consisting of three payments at each on-site visit. The research staff will also give each participant a reminder call or email for the initial session and each follow-up session. Each research staff member will be easily available for the participants to contact via email or phone. Participants need to provide informed consent. We will be asking each participant to answer questions about the consent form to determine that the study process and the duration of participation are completely understood by all participants. We will aim to have a specific research team member assigned to complete all sessions with the same participant. The study team will work hard at forming a professional relationship with the participant so they feel comfortable and willing to discuss what may be sensitive information. Participants will no longer be eligible to continue the study if they miss more than 2 stimulation sessions. Participants will be reimbursed \$30 per in-person visit, covering all travel expenses by the TTC.

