Eligible participants enrolled in this clinical trial will have a total of 28 visits. There will be 1 screening visits which will take place over the phone, 3 on-site visits (including 1 mask development visit, 1 mask delivery visit, and 1 very last follow-up visit) and 24 On-line visits (to take place over videoconference on Zoom platform); Baseline Visit (Visit 0), 20 days of the FES treatment sessions (Visits 1-20), and three post-stimulation visits (Visits 21-23). The screening Visit will take about 90- minutes, the on-site mask development visit will take 40 minutes and the mask delivery Visit will take 60-90 minutes. The baseline Visit (Visit 0) will take approximately 45 minutes, and treatment days (Visits 1-20) will take 60 min each (45 min for stimulation and 15 min for preparations). Sessions 5, 10, 15, and 20 will last about 105 minutes and will include similar clinical assessments/questionnaires to the baseline visit. The post-stimulation visits will take approximately 45 min. We estimate that the total participation duration will be approximately 33 to 35 hours.

Prior to the baseline visit, participants will undergo a screening evaluation that includes a medical/treatment history assessment and a confirmation of the MDD diagnosis. If all inclusion criteria are met, the mask development visit, the mask delivery visit, and the baseline visit will be scheduled. During Visit 0, medical assessments will be performed, and baseline assessments consisting of a semi-structured interview and self-report scales will be conducted. Once all baseline measures are collected, participants will be randomly assigned to one of two treatment arms:

- **ARM 1. 40 Hz FES:** 40 Hz Functional Electrical Stimulation (FES) stimulation, 45 mins per day for the duration of 4 weeks (20 sessions).
- **ARM 2. Sham FES:** 45 mins per day for the duration of 4 weeks (20 sessions).

Patients who miss a treatment visit, including due to statutory holidays, will be flagged in the database as non-adherent but will not be withdrawn from the study. They will still receive the entire treatment schedule but over a longer time period. However, if subjects miss more than two treatment days during treatment Days 1-20, they will be withdrawn.

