#### Mask Delivery Visit:

The mold-printing and mask-making procedure will take 10-15 hours. We will use standard 3D printing technologies to print the designed mold geometry. After 3D printing the rigid plastic mold, we will cast the flexible mask with slots for affixing the electrodes to the desired locations of the mask surface facing the skin, and then run the cables for connection to the stimulation system through slits on the flexible mask. The mask will also be equipped with at least two hook-and-loop elastic band and Velcro fasteners passing around the back of the head to hold the mask on the face during the stimulation period. The mask will have a flexible nose wire extracted from commercially available surgical masks to better fit the mask around the subject's nose. The mask customized for the subject will then be ready for mounting on the subject's face to perform the targeted stimulation. We will deliver the customized mask during an on-site visit to the user with instructions about how to put the mask on and apply the stimulation.

Due to the customized design for each person with all components integrated into it, we expect that the process of wearing the mask and using it would be very straightforward. The instructions of use will be provided to the participants in both written and verbal formats. The participant will turn on the unit. There will be an external box with four switches for the four channels. The switches control the stimulation in the set-up phase. They will be in the set-up position at the start. Once all 4 channels are adjusted, the participant can switch all of the channels to the ready position to start the stimulation for the session. They should note down their suggested stimulation intensities for the 4 channels. A test of FES with mask will be done in this visit to walk the participant through the procedure and answer all the questions. Participants will receive the mask preprogrammed stimulator, and webcam at the end of this Visit.

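### The missed-visit rule flags statutory holidays as non-adherence and has no exemption for days without a usable mask, so read literally both count towards mandatory withdrawal

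*Protocol*

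**What the plan says.** The limit of two missed sessions appears in four places in the Protocol.

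- Section 10.3 lists, among the reasons for which a participant will be discontinued: "The participant misses more than two treatment visits".
- Section 5.4: "Participants will no longer be eligible to continue the study if they miss more than 2 stimulation sessions".
- Section 6.1 first sets a flag: "Patients who miss a treatment visit, including due to statutory holidays, will be flagged in the database as non-adherent". The same sentence says that such a patient stays in the study, and the next says that the full schedule is then given over a longer period. The withdrawal rule follows: "However, if subjects miss more than two treatment days during treatment Days 1-20, they will be withdrawn".
- Section 6.3 (FES Visits) allows up to two misses and lets visits be added to reach the planned number, within a period that the investigator judges reasonable.

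None of the four makes the limit depend on why the session was missed.

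Section 9.2 (3D mask) foresees skin reaction, poor fit and damage, and answers each with a changed or new mask. Only for damage does it tell the participant to stop: "we would ask the user to stop wearing the mask". Small damage may be repaired. For large damage, "we can simply run the 3D printing step for a new mask mold and then create a new mask". Section 6.3 (Mask Delivery Visit) gives the time for the mask: "The mold-printing and mask-making procedure will take 10-15 hours". It describes handover of the first mask as follows: "We will deliver the customized mask during an on-site visit to the user".

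**The concern.** Section 8.1 makes dropout and protocol compliance primary outcomes, and the trial is also the first use of a prototype mask. A flag labelled non-adherent should describe what the participant did. Section 6.1 attaches it to statutory holidays, which no participant controls. Once holidays are in, staff applying the text have no basis for leaving out a day on which the study itself told the participant not to wear the mask. The electrodes are built into the mask, so without it there is no session.

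Two things are at stake. First, the stored flag mixes calendar, device and participant causes, and the planning of the larger trial needs these apart. Second, withdrawal on the third missed day ends treatment for someone who may be willing to go on. The trial then does not see whether the replacement mask is tolerated over the remaining sessions, although section 9.2 provides for that replacement.

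**Working it through.** The protocol gives no figure to reproduce here, so the check is the arithmetic of the rule.

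**Inputs from the Protocol**
- Withdrawal at more than two missed treatment days (5.4, 6.1, 10.3).
- Non-adherent flag at one missed visit, holidays included (6.1).
- 20 weekday sessions, five per week (6.3).
- Mask fabrication 10 to 15 hours (6.3).
- 20 participants (14.1).

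**Assumptions (not in the Protocol)**
- Days without a usable mask count as missed.
- Holidays count towards withdrawal as well as towards the flag.
- 0 to 2 statutory holidays fall within the treatment block.

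**Rule.** Let D be weekdays without a usable mask, H statutory holidays in the block, and O other misses. The participant is flagged if D + H + O ≥ 1 and withdrawn if D + H + O > 2.

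**Length of one remake.** If fabrication runs continuously, 10 to 15 hours is less than one day. On an assumed 8-hour working day it is 10/8 = 1.25 to 15/8 = 1.875 working days. Fabrication alone therefore costs at most about two weekdays. Any redesign and the wait for handover come on top, and neither is stated.

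**Result with O = 0**

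| Holidays H | D = 1 | D = 2 | D = 3 |
|---|---|---|---|
| 0 | flag only | flag only | withdrawn |
| 1 | flag only | withdrawn | withdrawn |
| 2 | withdrawn | withdrawn | withdrawn |

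A single remake of one or two weekdays with no holiday gives the flag and no more. A two-day remake plus one holiday gives 2 + 1 = 3, which is withdrawal, with no session missed by choice. Two remakes of two days each give 4, also withdrawal.

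**Do added visits cancel the miss?** Section 6.1 grants the longer schedule and then restricts it with the withdrawal sentence. Section 6.3 adds visits next to the same limit of two. Neither says that a made-up session stops counting as missed.

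**Effect on the primary outcomes.** One participant is 1/20 = 5 percentage points. One withdrawal takes compliance from 20/20 (exact 95% lower limit 83.2%) to 19/20 (75.1%). Neither reaches the lower limit above 90% that section 14.2 asks for, so the withdrawal changes the estimate and its meaning, not whether that criterion is met.

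**The case against.** A reader might infer that mask remakes will regularly force withdrawals, whether the mask is damaged, ill-fitting or irritating. The documents do not support that:

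- No section calls remake days missed visits, and the wording speaks of the participant missing.
- Holidays are named only in the flag sentence of 6.1, which also says that the patient is kept. That they count towards withdrawal as well follows from the sentence after it and from the lack of any exemption, but it is not spelled out.
- Only damage carries an instruction to stop. For a skin reaction or poor fit, 9.2 does not say whether the old mask is worn meanwhile. Fit is also tried with stimulation at the delivery visit, before session 1.
- Section 9.2 expects the material to be durable, and the stated fabrication time does not by itself reach a third missed weekday.

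A reader might also infer that the results could never separate device causes from participant causes. That goes too far. Sessions are held by videoconference with daily questions, the participant reports the damage, early withdrawals get a note to file (10.3), and deviations are logged with details (12.5). Much of the cause could be recovered. The flag would still be mislabelled, and sessions not given after a withdrawal would still be lost.

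Finally, a cap on missed sessions protects the dose, and counting device failure against compliance is the cautious choice for a take-home prototype. The cap is defensible and can stay. The caution is better served by reporting device downtime openly than by recording it as non-adherence.

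**Conclusion.** The point holds in a limited form, and its severity is minor. That a holiday sets the non-adherent flag is explicit in section 6.1. That holidays and study-ordered mask downtime also count towards mandatory withdrawal is the literal reading of four unqualified statements, but it is still a reading.

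The number of participants affected cannot be estimated, because the protocol gives neither a mask-failure rate nor a turnaround time beyond fabrication. What can be said is conditional: one lost weekday sets the flag; a third missed day from any mix of causes forces withdrawal; and each withdrawal moves compliance and dropout by 5 percentage points at 20 participants. How far the flag alone affects the compliance rate depends on whether a flagged participant who completes all 20 sessions is counted as compliant, which section 14.2 leaves open.

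**What to change.** In sections 5.4, 6.1, 6.3 and 10.3, use the same wording to state that statutory holidays and days without a usable mask for study or device reasons neither set the non-adherent flag nor count towards the limit of two. Let the schedule extend for those days up to a fixed cap, for example 20 sessions within 6 weeks. Record a reason for each missed session, and report device downtime by arm as its own feasibility result, so that the exemption does not hide device failures.

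The cost is a few sentences in four sections and one reason field, with no extra participants or staff. The downside is a somewhat longer and less uniform treatment period for those affected: with the example cap, up to 6 − 4 = 2 weeks more.

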#### Functional Electrical Stimulation Improves Symptoms of Major Depressive Disorder

Kapadia et al. (2019) conducted a follow-up open-label mixed-methods study on individuals with MDD, where they wanted to explore whether 10 sessions of the FES would lead to improvements in depressive symptoms. This study recruited 10 individuals with moderate-to-severe MDD, and all study participants received facial FES of the “Duchenne” muscles three times per week for a minimum of 10 sessions and a maximum of 40 sessions. All participants received 10 sessions of the FES and were invited to continue therapy for up to 40 sessions if they wished (5 out of 10 participants requested to undergo 40 FES sessions). The results were promising: participants experienced early improvements in depressive symptoms as measured by the Hamilton Depression Rating Scale (HAM-D) and Inventory of Depressive Symptomology (IDS) upon

completing 10 sessions of treatment. On average, the participants showed an improvement on the HAM-D by 8.1 points (SD = 5.26,  $p = .005$ ) and on the IDS by 14 points (SD = 11.05,  $p = .008$ ). Eighty percent of participants showed a reduction by at least 30%, 50% achieved clinical response (i.e., change in the HAM-D by at least 50%), and 60% entered remission. The reported adverse events were insignificant, involving commonly reported redness or skin irritation underneath the stimulation site, muscle soreness, and muscle discomfort. All participants enrolled in the trials adhered to the treatment protocol, showing high compliance. FES was well-tolerated, with the potential to be administered with limited physician oversight.

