### Dosing, adverse effects, and contraindications

To understand the optimal dosing or adverse events associated with the FES, certain studies have shown that a minimum of 20 FES sessions were needed to detect a change in function, and 40 FES sessions were needed to see a change in the quality of life. Regarding the tolerability

and safety of the FES, no significant adverse events have been noted. Common mild adverse events include redness below the area of the electrodes, which typically dissipates within 24 hours, and occasional muscle fatigue or soreness, which also typically resolves without intervention within 24 hours.

The use of FES in a therapeutic setting is associated with certain contraindications, which include metal implants at the stimulation site, pacemakers, open wounds or rash at the electrode placement site, and uncontrolled autonomic dysreflexia. The FES target muscles have to be accessible for placement of the stimulation electrodes – for example, transcutaneous FES can be delivered with a greater level of specificity when the target muscles are more superficial (e.g., flexor carpi ulnaris, flexor carpi radialis), while for deeper muscles, eliciting an isolated contraction without stimulating the overlying muscles (e.g., flexor digitorum profundus) might be more challenging. Certain muscles, such as the iliopsoas, cannot be stimulated using surface electrodes due to their anatomical location. Furthermore, the degree of lower motor neuron injury or nerve root damage of the stimulated muscle must not be significant. Finally, the patient must be cognitively able to follow the instructions and actively participate in the therapy process for the maximal therapeutic benefit from the FES.

While the FES devices are portable, a home-based study to examine efficacy and tolerability is essential as all compliance will be monitored and intervention delivered under observation by a physiotherapist or a trained investigator. Therefore, besides investigating the feasibility and efficacy of FES, we will develop a prototype for a home-based device with a cast-molded personalized Mask on a 3D printed mold and programmable stimulator to enable self-administration.

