#### Exclusion Criteria

Patients will be excluded if they:

1. Have a history of epilepsy or seizures

2. Have any paralysis of facial nerves
3. Have metallic implants in the mouth or metal braces near the potential sites of electrical stimulation, and any type of implanted electronic devices (insulin pump, pacemaker...)
4. Have current fibromyalgia or currently receiving or have received rTMS within the last month (28 days) before screening
5. Have any past or current symptoms of mania, hypomania, mixed episodes, psychotic disorders, active substance abuse, or dependence (excluding nicotine and caffeine), which will be confirmed on the MINI done by a trained research assistant
6. Have current suicidal intent or plan as demonstrated by a score of  $\geq 2$  on MADRS item 10.
7. Are unable to understand instructions in English
8. Are unable to produce the “Duchenne marker” expression (see “Procedures” for details) with FES, secondary to any type of neurological condition or previous botulinum toxin treatments of facial muscles
9. Pain in the body part being tested (measured and/or stimulated)
10. Skin lesion at a site of stimulation electrodes or motion sensors
11. Any type of bone fracture
12. Females who are pregnant or planning to become pregnant throughout the duration of the study.
13. Active deep vein thrombosis
14. Cancer or radiation in the past 6 months
15. Uncontrolled autonomic dysreflexia
16. Orthostatic hypotension
17. Botulinum toxin injection into muscles targeted by the stimulation in the past 6 months

**Justifications for any exclusions based on race, gender, or ethnicity:** non-English speaking individuals are excluded because the ability to accurately and completely communicate study information, answer questions about the study, and obtain consent are necessary.

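### Read literally, section 10.3 makes newly developed pain at the stimulated site a mandatory withdrawal, with no exemption for the mild, self-resolving soreness the protocol expects from FES

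*Protocol*

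**What the plan says.** The withdrawal list in Protocol section 10.3 opens with "A study participant will be discontinued from further participation if". One item on it reads "The participant meets any exclusion criteria (either newly developed or not previously recognized". The wording is mandatory, covers every exclusion criterion, and has no exception for effects of the treatment itself. Investigator judgement appears as a separate item, which can add withdrawals but cannot waive one.

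Two criteria in section 5.1 concern the stimulated site. Criterion 9 is "Pain in the body part being tested (measured and/or stimulated" and criterion 10 is "Skin lesion at a site of stimulation electrodes or motion sensors". Neither has a threshold.

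Section 3 describes what FES is expected to do. Of the earlier pilot in MDD it says: "The reported adverse events were insignificant, involving commonly reported redness or skin irritation underneath the stimulation site, muscle soreness, and muscle discomfort". It adds: "All participants enrolled in the trials adhered to the treatment protocol, showing high compliance". Its paragraph on dosing and adverse effects lists "occasional muscle fatigue or soreness, which also typically resolves without intervention within 24 hours". Section 9.2, on the earlier healthy-volunteer and MDD studies, says instead "we saw (i) no safety concerns and (ii) no AEs".

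**The concern.** Criterion 9 is sensible at screening, because someone who already has facial pain should not start. Section 10.3 carries it unchanged past randomization, where it can catch a short-lived effect of the treatment under test. Adverse effects are reviewed before and after every session (section 6.3), so even brief soreness is likely to be noticed and recorded.

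Dropout is one of the primary feasibility outcomes (section 8.1). Hypothesis 1c in section 4 says that the nature of adverse events will not materially affect dropout, yet the rule can make one kind of adverse event a dropout by definition. The observed rate would then partly measure the rule and only partly tolerability. Hypothesis 1a, that dropout is similar between arms, is also exposed if soreness is more common with motor-level current than with the sensory-level sham.

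**Working it through.** The check is mainly a comparison of text. The protocol states no figure that needs reproducing.

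**Step 1. Does the rule reach an expected effect?**
- Rule (10.3): mandatory, any exclusion criterion, newly developed ones included.
- Criterion 9 (5.1): pain at the stimulated site, without limit.
- Expected effect (3): muscle soreness and discomfort, usually gone within a day without treatment.

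The three connect only if soreness counts as pain. The protocol does not define pain, so that reading is open but not forced.

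**Step 2. Do other sections agree with the rule?**
- Section 6.3: when a participant has difficulty, staff try to lessen the burden.
- Section 9.2: a skin reaction leads to another mask material, and discomfort from poor fit leads to a modified mask.
- Section 11.2.3: the mild grade covers transient discomfort that needs no treatment.

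All three assume that the participant continues. Under the literal reading, section 10.3 gives the opposite instruction.

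**Step 3. What is one rule-driven withdrawal worth?**
Inputs: N = 20 (section 14.1), 1:1 allocation (section 6.2), so 10 per arm if the arms are balanced.
- Overall dropout: 1/20 = 5 percentage points.
- Within one arm: 1/10 = 10 percentage points.
- For scale, the 15% dropout allowance in section 5.3 is 0.15 × 20 = 3 participants.

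**Step 4. How many could there be?**
No soreness rate is given. As an assumption, let r be the share of the 10 active participants who are sore at least once, and suppose that the literal rule withdraws each of them. Expected withdrawals are 10r, and the chance of at least one is 1 − (1 − r)^10.
- r = 0.10: 1 withdrawal, 5% of 20; chance of at least one 0.651.
- r = 0.30: 3 withdrawals, 15% of 20; chance 0.972.
- r = 0.50: 5 withdrawals, 25% of 20; chance 0.999.

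If sham participants were also sore, at an assumed 10%, one more expected withdrawal would be added to each line.

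The rule applies at every session, so a small risk accumulates. With a per-session risk q, and sessions assumed independent, the risk over 20 sessions is 1 − (1 − q)^20. For q = 0.01, 0.02 and 0.05 this is 18%, 33% and 64%.

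These lines show how sensitive the outcome is. They do not predict what will happen.

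**Step 5. Section 9.2 against section 3.**
Section 9.2 says that the two earlier studies saw no AEs, while section 3 lists AEs from the MDD study. The next sentence of section 9.2 itself names irritation, soreness and discomfort and cites the same two studies among its sources. The phrase is therefore wrong within its own paragraph.

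**The case against.** The strongest reply is that the protocol never describes an FES effect as pain. It speaks of redness, irritation, soreness, discomfort and fatigue. Read as a whole, with the provisions in sections 6.3, 9.2 and 11.2.3, it plainly means mild effects to be managed. This stands in part: withdrawal for every sore participant is not certain. It does not remove the problem, because staff must then apply an unwritten threshold or depart from a mandatory rule, and a primary outcome depends on which they do.

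Section 10.3 also already provides for safety data on participants discontinued for an AE, questions about their FES experience, and a note to file. Rule-driven withdrawals could therefore be identified afterwards. That helps interpretation but does not bring the participants back. Stopping for genuine pain is itself tolerability information, and the fix should preserve it.

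A reader might infer more than the documents support:
- **That expected mild effects are necessarily dropouts.** This depends on reading soreness as pain.
- **That dropout would rise from 15% to 30%.** This adds three assumed withdrawals to the allowance of three in section 5.3. That allowance is an overall figure and is not stated to exclude withdrawals for adverse events.
- **That the burden falls on the active arm.** Active current is 1-25 mA and sham 1-8 mA, which makes an imbalance plausible. But section 6.2 sends automated messages to both arms, and section 6.3 asks for voluntary smiling during stimulation without limiting this to the active arm. Sham participants may be sore too.
- **That section 9.2 conceals the effects.** Its next sentence lists them.
- **That redness meets criterion 10.** Whether redness is a lesion is doubtful, and the point does not need it.

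**Conclusion.** The point holds as a defect of wording with a real but unquantified effect. Section 10.3 can turn an expected, self-resolving effect into a mandatory withdrawal, and it conflicts with how the rest of the protocol treats such effects. The firm figure is 5 percentage points of overall dropout per withdrawal at N = 20. The total is unknown: the 5% to 25% range rests on assumed soreness rates of 10% to 50% in the active arm, no soreness in the sham arm, and withdrawal of everyone affected. A difference between arms is possible but not established. The no-AEs phrase in section 9.2 is a separate, minor factual error that stands however pain is read.

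**What to change.** In section 10.3, state that after randomization criterion 9 does not apply to mild, transient FES-related soreness or discomfort: mild as graded in section 11.2.3, and resolving within about 24 hours as section 3 expects. Such events are recorded as AEs and the participant continues. Pain that is moderate or severe, that persists, or that is not related to FES still leads to discontinuation.

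Keep criterion 10 in force throughout. Section 3 names open wounds or rash at the electrode site as contraindications, and treatment is self-applied at home, so limiting that criterion to screening would remove a needed safety stop.

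In the existing early-withdrawal note to file, record which item of section 10.3 applied. In section 9.2, replace the statement of no AEs with the mild effects reported in section 3.

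The cost is one clause, one line in an existing note and one corrected phrase, with no new visit, form or analysis. The downside is a slightly less automatic stop for mild soreness, and the investigator-judgement item remains available for any case that looks unsafe.
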